## Abstract

**Background:**

Chronic musculoskeletal pain (CMP) imposes a significant psychological, physical, and emotional burden on millions of adults in the United States. A challenge in treating CMP is its tendency to become enmeshed with a person’s sense of self. Mindfulness-based interventions (MBIs) offer a promising approach to help patients disentangle pain from their sense of self. However, rigorous research is needed to determine which styles of mindfulness practice most effectively promote self-transcendence, a candidate mechanism for durable pain relief.

**Objective:**

This study aims to evaluate whether adding direct pointing instruction to traditional mindful breathing enhances self-transcendence and pain relief. We will assess the effects of 2 mindfulness training protocols, mindful breathing (MB) and MB plus direct pointing (DP) instruction, on subjective and neurophysiological markers of self-transcendence and on pain-related outcomes.

**Methods:**

In this study, we will conduct a 3-arm randomized controlled trial with 173 adults with CMP, assigned to one of the following groups: (1) 4, 30-minute sessions of traditional mindful breathing instruction, (2) 4, 30-minute sessions of MB+DP instruction, or (3) a waitlist control group. Self-transcendence will be assessed during the first and final intervention sessions using validated self-report measures and psychophysiological indices, including electroencephalography (EEG; theta activity) and functional near-infrared spectroscopy (fNIRS; default mode network [DMN] activity). Primary outcomes include changes in self-transcendence, theta activity, and DMN activity. Additional outcomes include acute pain intensity and pain-related functional interference, measured at baseline through 3-month follow-up.

**Results:**

Data collection began in October 2024 and will conclude by May 2027. As this is a protocol paper, no results are yet available. We will report recruitment rates, baseline characteristics, and initial outcome trends in the full trial results paper.

**Conclusions:**

This will be the first randomized controlled trial to examine whether direct pointing instruction enhances analgesia by eliciting self-transcendence. Findings may advance understanding of the mechanisms underlying mindfulness-based pain relief and inform the development of more targeted MBIs for chronic pain. Results will be disseminated through peer-reviewed publications, conference presentations, and stakeholder engagement, with potential implications for clinical practices.

## Introduction

### Background

Chronic musculoskeletal pain (CMP) is among the most prevalent and disabling health conditions worldwide, affecting up to one-third of the global population and significantly diminishing quality of life and workplace productivity [1-3]. In the United States, CMP is a major contributor to health care expenditures and long-term disability [1,2,4]. Given the well-documented risks associated with pharmacologic treatments, such as gastrointestinal complications from nonsteroidal anti-inflammatory drugs and the potential for addiction and overdose with opioid analgesics, guidelines from the American College of Physicians recommend nonpharmacologic treatments, such as massage, acupuncture, and mindfulness, as preferred first-line therapies for managing CMP [5]. Nonpharmacologic approaches not only offer a safer alternative to pharmacologic treatment but also more directly address the complex biopsychosocial factors that contribute to chronic pain [6]. Among the notable psychological consequences of chronic pain is its potential to alter an individual’s sense of self [7-9]. Persistent pain may become enmeshed with personal identity through repeated and simultaneous activation of self- and pain-related schemas (eg, “I am [ie, self-schema] in pain [ie, pain schema]”) [7]. Over time, this repeated activation leads to a pain-laden self-concept [8,10,11] which may be reflected in corresponding changes within the brain’s default mode network (DMN) [12-14]. The DMN is a system involved in both self-representation and pain processing, potentially trapping individuals in a self-perpetuating “pain perception box” [7,10,11].

Mindfulness-based interventions (MBIs) offer a promising means of disentangling chronic pain from the sense of self, thereby disrupting the maladaptive cycle that sustains the pain individuals endure [9]. Rather than providing mere distraction or placebo effects, mindfulness engages specific neural and psychological mechanisms that fundamentally alter pain perception and appraisal [15-17]. Central to this process is a reduction in self-referential processing, a shift supported by neuroimaging evidence showing decoupling between the thalamus and DMN hubs such as the precuneus and medial prefrontal cortex during mindfulness practice [9,15,18,19]. This decoupling may represent a loosening of the neural circuits that enmesh pain in the sense of self, facilitating a more open, present-centered awareness [9,15,18,19]. The Mindfulness-to-Meaning Theory deepens this perspective by suggesting that mindfulness initiates a recursive cycle of positive psychological processes, including decentering, attentional broadening, cognitive reappraisal, and savoring, that synergistically promote self-transcendent states [9]. These transient states, characterized by diminished self-salience and expansive positive affect (eg, awe, bliss, and compassion), weaken the cognitive and emotional enmeshment between the individual and their pain experience [9,20]. Through momentary dissolution of the subject-object dichotomy, self-transcendence can reduce the centrality of pain in consciousness and cultivate a renewed sense of meaning [9,20]. In this way, mindfulness-induced self-transcendence may not only reshape the brain’s functional architecture but may also reframe the lived experience of pain, offering a path toward relief that is both neurologically grounded and psychologically liberating [9].

Emerging empirical evidence supports this theoretical framework. Two randomized controlled trials (RCTs) have examined the therapeutic value of self-transcendent states elicited during brief (ie, 15-20-minute), single-session mindfulness-based interventions (MBIs) for adults undergoing knee or hip replacement surgery (n=196, n=118) [21]. In both RCTs, the MBIs incorporated direct pointing (DP), an ancient yet underexplored contemplative technique designed to evoke self-transcendence by guiding attention away from self-specifying information and toward the nature of awareness itself [22-24]. Specifically, DP instruction encourages deidentification with thoughts, emotions, sensations, and sensory input as a means of accessing a nondual form of awareness in which the usual subject-object distinction dissolves [22-24]. Across both RCTs, groups involving mindfulness paired with DP consistently evoked the highest levels of self-transcendence relative to the psychoeducation control group, which in turn predicted immediate pain relief and improved postoperative outcomes, including reduced pain intensity and interference during the first month after surgery and better physical functioning 6 weeks after surgery [21,25,26]. These findings highlight the potential of DP to enhance the analgesic effects of brief MBIs by targeting self-related mechanisms of pain. However, because all mindfulness groups in these RCTs included DP instruction, the specific contribution of this technique remains to be isolated.

The therapeutic value of self-transcendence has also been examined in 4 RCTs evaluating the 8-week Mindfulness-Oriented Recovery Enhancement (MORE) program as a treatment for adults with chronic pain receiving long-term opioid therapy (n=95, n=187, n=62, and n=165) [27-30]. MORE incorporates DP throughout its protocol and has been shown to increase self-transcendent experiences both in daily life [27,30] and during lab-based, self-guided mindfulness practice [28,29]. In these RCTs, self-transcendent experiences were associated with reductions in pain, opioid misuse, and opioid dosing out to 9-month follow-up, as well as increases in frontal midline theta activity, which is thought to be a neurophysiological marker of meditative absorption and self-dissolution [27-30]. Collectively, these findings suggest that self-transcendence, along with its neurophysiological correlates, may serve as a core mechanism through which mindfulness improves chronic pain-related outcomes. Yet, due to the multimodal nature of MORE, the specific effects of DP remain confounded and warrant further investigation.

### Aims

To isolate the specific effect of DP to mindfulness-based pain relief, the Pointing Beyond project will randomize 173 adults with CMP into one of three groups: (1) 4 weekly 30-minute sessions of traditional mindful breathing (MB) instruction, (2) 4 weekly 30-minute sessions of MB combined with DP (MB+ DP) instruction, or (3) a waitlist control group (WLC). The specific aims are:

#### Aim 1

Evaluate between-group differences in changes in self-transcendence from Session 1 to Session 4 across the MB, MB+DP, and WLC groups, using a validated self-report instrument (state version of the Nondual Awareness Dimensional Assessment [NADA-S]; primary outcome) and 2 psychophysiological indices (secondary outcomes), including frontal midline theta activity (via electroencephalography [EEG]) [28,29] and a functional near-infrared spectroscopy (fNIRS) [31] derived proxy default mode network (DMN) activity.

#### Aim 2

Examine the associations among phenomenological and psychophysiological indices of self-transcendence by testing within- and between-session correlations between self-reported self-transcendent state (NADA-S), frontal midline theta activity (EEG), and fNIRS-derived proxy DMN activity across intervention sessions and study groups.

#### Aim 3

Determine whether increases in self-transcendence mediate treatment-related improvements in pain outcomes by testing indirect effects of group assignment (MB, MB+DP, and WLC) on (1) acute pain intensity at the end of Session 4 (secondary outcome) [32] and (2) pain-related outcomes (eg, functional interference) through 3-month follow-up (tertiary outcomes) [33-38], via changes in (1) self-reported self-transcendence (NADA-S), (2) frontal midline theta activity (EEG), and (3) fNIRS-derived DMN activity measured during Session 4, controlling for presession pain and baseline levels of the mediators.

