### Hypotheses

The following are our hypotheses:

#### Aim 1

We hypothesize that, from Session 1 to Session 4, both mindfulness groups (MB and MB+DP) will show greater increases in self-transcendence, indexed by higher NADA-S scores and greater frontal midline theta activity (EEG), and greater decreases in DMN activity, indexed by reduced fNIRS-derived fronto-temporal-parietal connectivity, compared to WLC group. We further hypothesize that MB+DP will produce larger increases in these phenomenological and neurophysiological indices of self-transcendence, and larger reductions in DMN activity, relative to MB alone.

#### Aim 2

We hypothesize that phenomenological and psychophysiological indices of self-transcendence will be significantly and coherently related across sessions and groups, such that a higher self-reported self-transcendent state (NADA-S) will be associated with greater frontal midline theta activity (EEG) and lower fNIRS-derived proxy DMN activity within sessions and across Sessions 1-4. We further hypothesize that these associations will be the strongest in the MB+DP group, intermediate in the MB group, and the weakest or absent in the WLC group, reflecting graded coupling between subjective experience and neural indices of self-transcendence as a function of mindfulness instruction type.

#### Aim 3

We hypothesize that treatment-related improvements in pain outcomes will be mediated by increases in self-transcendence and its psychophysiological correlates. Specifically, we expect that assignment to the mindfulness groups, particularly MB+DP, will be associated with lower acute pain intensity at the end of Session 4 and reduced pain-related functional interference through 3-month follow-up via (1) increases in self-reported self-transcendent state (NADA-S), (2) increases in frontal midline theta activity (EEG), and (3) reductions in fNIRS-derived proxy DMN activity measured during Session 4, controlling for presession pain and baseline levels of each mediator [39,40].

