Second, to enhance the clinical interpretability of the intervention effects, we added a waitlist control group. This adjustment was made prior to participant enrollment. Inclusion of this no-treatment comparison group provides a benchmark against which to evaluate the specific impact of the MBIs on both mechanistic and clinical outcomes, relative to the natural progression of symptoms in the absence of additional intervention. This control arm was designed to be half the size of each active treatment group (n=35), resulting in a total sample size of 173 and preserving a 2:2:1 randomization ratio. This total sample size (n=173) is consistent with a G*Power estimate for a 3 (group)×2 (time) mixed design, assuming a small effect (Cohen *d*=0.30), 80% power, and a Bonferroni-adjusted alpha of .0125 for 4 pairwise comparisons (ie, self-reported self-transcendence; 2 psychophysiological indices of self-transcendence, including frontal midline theta activity and DMN activity, and acute pain). Beyond these primary group-level effects, the planned sample size also supports Aims 2 and 3. Specifically, a G*Power analysis (2-tailed, *α*=.0167, corrected for multiple comparisons; power=0.80) indicated that 112 participants are sufficient to detect a moderate association (*r*=0.30) among phenomenological and psychophysiological indices of self-transcendence, well below the planned sample of n=173. Finally, this sample size is adequate for the planned mediation analyses; the parallel multiple-mediator model for acute pain includes 19 estimated parameters, yielding approximately 9.1 observations per parameter with n=173, consistent with the commonly cited 5‐10 observations per parameter convention.

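### Aim 2's headline correlation runs across three arms that Aim 1 expects to differ on every index, so it can be significant with no coupling inside any arm

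*Protocol article*

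**What the plan says.** The Aims section defines Aim 2 as within- and between-session correlations among self-reported self-transcendence, theta and "fNIRS-derived proxy DMN activity across intervention sessions and study groups". Under Hypotheses, the first Aim 2 statement is that the indices "will be significantly and coherently related across sessions and groups". A second statement follows: "We further hypothesize that these associations will be the strongest in the MB+DP group, intermediate in the MB group", and weakest or absent in WLC.

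The Participants section supports Aim 2 with one calculation. A two-tailed test at .0167 with power 0.80 "indicated that 112 participants are sufficient to detect a moderate association" of r = 0.30, and this is compared with the planned 173, which is all three arms together. No arm or session term is attached to Aim 2 there or under Statistical Analysis. Aim 3, in contrast, names its covariates.

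The Aim 1 hypothesis is that "both mindfulness groups (MB and MB+DP) will show greater increases in self-transcendence, indexed by higher NADA-S scores and greater frontal midline theta activity", with DMN connectivity falling, compared with WLC. It adds that "MB+DP will produce larger increases in these phenomenological and neurophysiological indices of self-transcendence, and larger reductions in DMN activity, relative to MB alone".

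**The concern.** If Aim 1 is right, arm is a common cause of all three indices. NADA-S and theta rise together from WLC to MB to MB+DP while connectivity falls. These are the signs that Aim 2 looks for: positive with theta, negative with DMN. A correlation taken over all participants adds this between-arm covariance to whatever person-level association exists. It can therefore be significant when, inside each arm, people with higher NADA-S have no more theta and no less connectivity than others. Where sessions are combined, session means act in the same way.

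This bears on interpretation. The Discussion relies on agreement between self-report and the neural indices to answer the worry about demand characteristics and to strengthen the causal reading of the mechanism. Suppose that demand raised NADA-S in the active arms while practice raised theta there for unrelated reasons. The pooled correlation would still be positive.

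**Working it through.** **1. The plan's own figure.** Inputs from Participants: r = 0.30, two-sided alpha .0167, power 0.80. By Fisher's z:

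n = ((z for alpha/2 + z for power) / atanh(r))² + 3 = ((2.393 + 0.842) / 0.3095)² + 3 = 112.2.

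A bias-corrected version gives power 0.802 at n = 112 and 0.797 at n = 111. The stated 112 is right. The question is what the correlation measures.

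**2. Correlation from arm means alone.** Allocation is 2:2:1 (69 MB, 69 MB+DP, 35 WLC). Take within-arm SD 1 and within-arm correlation 0 on both indices, with equal standardized arm means m on both (sign reversed for DMN). Then

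pooled r = V / (1 + V), where V is the weighted variance of the arm means.

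Example with rounded weights .2/.4/.4 and means 0/0.6/1.2: the mean is 0.72, the mean square is 0.4 × 0.36 + 0.4 × 1.44 = 0.72, so V = 0.72 − 0.5184 = 0.2016 and r = 0.2016 / 1.2016 = 0.168.

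**3. Rejection rates under zero within-arm correlation.** These come from 20,000 simulated trials per setting, two-sided at .0167. N = 138 is 173 × 0.80, which carries over the 110-to-138 attrition allowance. The steps between arms use d = 0.30 (the planning value) and d = 0.60 (the smallest preliminary effect). Their placement between arms is my assumption.

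| Means WLC/MB/MB+DP (SD) | Pooled r | Rejects, N = 138 | Rejects, N = 173 |
|---|---|---|---|
| 0/0.3/0.6 | .05 | 3.5% | about 4% |
| 0/0.6/0.9 | .10 | 10.5% | 13–14% |
| 0/0.6/1.2 | .17 | 34% | 44% |

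Nominal is 1.67%. With unequal shifts (0/0.6/1.2 on NADA-S, 0/0.3/0.6 on the physiological index) r is .09 and the rate at N = 173 is 11%. Arm means alone reach the planning value r = 0.30 only at about 0.87 SD per step.

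**4. After centring on arm means.** The mean r is 0.00 and the rejection rate is 1.5 to 1.8% in every setting tried. With a true within-arm r of 0.30, power at N = 173 is about 0.95.

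**5. Arm-specific correlations.** Power for r = 0.30 at .0167 is about .55 at n = 69 and .26 at n = 35.

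**6. Main effects of arm and session are not enough.** Aim 1 predicts a difference in change from Session 1 to Session 4, which is an arm-by-session effect. In a change-score analysis the arm main effect cancels and the session effect becomes the intercept, so the arms are pooled again. With a within-person correlation of .5, the SD of change is √(2 × (1 − .5)) = 1. Change shifts of 0/0.6/0.9 then give the same inflation as in step 3: about 13 to 14% at N = 173. Adding arm-by-session brings it back to 1.6%.

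**The case against.** - **The reading.** Across sessions and groups could mean examined in each session and group, and the article gives no Aim 2 model. The analysis plan is not shown and may carry an arm term. The comparison of 112 with 173 cannot settle whether arm is adjusted for, because an adjusted test would need almost the same number (about 114). This stands as a limit on certainty. It does not remove the point: the aim, its first hypothesis and its sample size all describe an association over the whole sample with no arm term.
- **Aim 2 already holds an uncontaminated test.** Correlations inside one arm are free of arm means, and an association made only of arm means would not show the predicted grading across arms. This stands as mitigation. However, it is a further hypothesis with no sample size, and power is low even to detect r = 0.30 in one arm.
- **The estimand.** Indices that move together because of randomized instruction are, literally, "significantly and coherently related across sessions and groups". Rejection is a false positive only if the target is coupling between people within an arm, or within a person. That is fair. But the second Aim 2 hypothesis speaks of coupling, and the Discussion wants evidence that goes beyond self-report. A correlation of arm means cannot supply it.
- **Size.** The documents do not give arm separation for all three indices. At d = 0.30 per step the inflation is only about twofold.

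A reader might infer that the 112 is wrong, that Aim 2 has no valid test of coupling, or that gross inflation follows from the plan's own effect size. The documents support none of these. The 112 reproduces, the arm-specific hypothesis exists, and rates above 30% need about 0.6 SD per step.

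**Conclusion.** The concern holds as a matter of what the headline Aim 2 correlation can show. As stated, it covers all three arms with no adjustment, while Aim 1 expects that "both mindfulness groups (MB and MB+DP) will show greater increases in self-transcendence" and that MB+DP exceeds MB. A significant pooled result may therefore only repeat Aim 1. Against a nominal 1.67%, the rejection rate without within-arm coupling is about 3.5–4%, 10–14% or 34–44% in the three settings tabulated. This rests on three assumptions: that the test pools the arms unadjusted, that the standardized shifts are equal on both indices, and that the arm steps lie between d = 0.30 and d = 0.60. If Aim 1 is false and the arms do not separate, the problem disappears. The point deserves correction but does not touch the primary outcome.

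**What to change.** State the Aim 2 estimand and adjust for arm, session and arm-by-session:

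- For the between-person association, use a within-session partial correlation given arm.
- For within-person coupling, use the association of person-centred or change scores given arm.
- Where sessions are combined in one model, add a participant random effect and keep the arm-by-session term. Arm and session main effects alone leave the bias in place.
- Report the unadjusted pooled correlation as description only.
- Keep the arm-specific associations, and acknowledge their limited power.

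The cost is a change of wording and a few degrees of freedom. The required N for r = 0.30 goes from 112 to about 114, well within 173 and within 138 after attrition.

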### Hypotheses

The following are our hypotheses:

#### Aim 1

We hypothesize that, from Session 1 to Session 4, both mindfulness groups (MB and MB+DP) will show greater increases in self-transcendence, indexed by higher NADA-S scores and greater frontal midline theta activity (EEG), and greater decreases in DMN activity, indexed by reduced fNIRS-derived fronto-temporal-parietal connectivity, compared to WLC group. We further hypothesize that MB+DP will produce larger increases in these phenomenological and neurophysiological indices of self-transcendence, and larger reductions in DMN activity, relative to MB alone.

#### Aim 2

We hypothesize that phenomenological and psychophysiological indices of self-transcendence will be significantly and coherently related across sessions and groups, such that a higher self-reported self-transcendent state (NADA-S) will be associated with greater frontal midline theta activity (EEG) and lower fNIRS-derived proxy DMN activity within sessions and across Sessions 1-4. We further hypothesize that these associations will be the strongest in the MB+DP group, intermediate in the MB group, and the weakest or absent in the WLC group, reflecting graded coupling between subjective experience and neural indices of self-transcendence as a function of mindfulness instruction type.

#### Aim 3

We hypothesize that treatment-related improvements in pain outcomes will be mediated by increases in self-transcendence and its psychophysiological correlates. Specifically, we expect that assignment to the mindfulness groups, particularly MB+DP, will be associated with lower acute pain intensity at the end of Session 4 and reduced pain-related functional interference through 3-month follow-up via (1) increases in self-reported self-transcendent state (NADA-S), (2) increases in frontal midline theta activity (EEG), and (3) reductions in fNIRS-derived proxy DMN activity measured during Session 4, controlling for presession pain and baseline levels of each mediator [39,40].

